#### Concealment mechanism {16b}

No one in the study team will be able to predict or influence who will receive an offer to join the intervention or know the allocation sequence in advance, as this is run iteratively after each baseline completion.

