### Who will take informed consent? {26a}

We will use online and offline recruitment channels (see SPIRIT item 15 for further details). Participants will be given a participant information leaflet describing essential information about the study. Potential participants will reply to an ‘expression of interest’ form, including self-reporting of eligibility. Additionally, contact information for the research team will be provided within the participant information leaflet and expression of interest, encouraging to make contact if they have questions. Based on preferences, the consent form will be delivered by post or through Nettskjema (UiO, Oslo) for those engaging online. Before providing consent, potential participants must confirm that they have read and understood the participant information leaflet. After receiving the consent form, a trial working group member will phone participants to confirm eligibility before inviting the participant to complete a baseline questionnaire. After completing the baseline questionnaire, one-in-three people will be randomly selected to be offered the intervention. The initial cohort study consent form will request consent to be approached for the intervention. A member from the trial working group will contact those selected by phone, providing information and to ask if they have any questions and if they might like to participate. An email or post package, based on their previous preferences, will be sent to those interested after the call, and contain a participant information leaflet describing the intervention and a consent form. If there is no response to the phone call, the email or post package will note that a member from the trial working group will contact by phone to ask if the participant has any questions or requires further information. The participant information materials and informed consent form are available from the corresponding author on request.

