#### Strategies to improve adherence to interventions {11c}

##### Participant adherence

To increase adherence to data collection and decrease the risk of dropout, participants will be given reminders, and their response rates will be monitored by the trial manager. The trial manager will be responsible for reminding participants of data collection appointments and being available to answer questions and concerns. Participants in the intervention group will be matched with a case manager who provides support throughout the 6-week placement and will answer any questions the participant may have about the intervention.

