### Assignment of interventions: allocation

#### Sequence generation {16a}

Randomisation will feature minimisation and be automated using a mix of Stata scripting (StataCorp, College Station, TX) and bash programming to keep personal data encrypted. The research team developed the minimisation script which at its core features the Stata program rct_minim [62, 63]. The first participant is randomly allocated with equal probability, and then for each subsequent participant, there is a two-thirds probability that allocation will be to the group that best minimises the imbalance on the selected factors (i.e. gender on three levels (male, female, or prefer not to say) and three levels of age (18 to 29, 30 to 49, and 50 and over)) [64–66].

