#### Implementation {16c}

The trial manager will run the script at least twice a week, and in cases where cohort participants are allocated to the intervention, the trial manager will retrieve contact information and give an invitation to participate in the intervention (see SPIRIT item 26a).

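### The protocol says no one can predict or influence allocation, but its minimisation procedure leaves assignments partly predictable; any resulting bias is likely small

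*Protocol article*

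**What the plan says.** Concealment mechanism {16b} makes an unqualified statement: "No one in the study team will be able to predict or influence who will receive an offer to join the intervention". Its reason is that "this is run iteratively after each baseline completion".

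The neighbouring sections describe the procedure:

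- **Sequence generation {16a}:** "Randomisation will feature minimisation and be automated using a mix of Stata scripting" and bash. After a first allocation at equal probability, "there is a two-thirds probability that allocation will be to the group that best minimises the imbalance on the selected factors". The factors are "gender on three levels (male, female, or prefer not to say) and three levels of age".
- **Implementation {16c}:** "The trial manager will run the script at least twice a week, and in cases where cohort participants are allocated to the intervention", that same person retrieves contact details and issues the invitation.
- **Who will be blinded {17a}:** staff directly involved in the trial are not blinded.
- **Who will take informed consent {26a}:** before baseline, "a trial working group member will phone participants to confirm eligibility before inviting the participant to complete a baseline questionnaire".
- **Data management {19}:** the working group has access to the stored data.

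**The concern.** Running minimisation one person at a time means that no list exists in advance. It does not make the next assignment unpredictable, because the favoured group follows from past allocations and two easily known characteristics. Nor does it rule out influence. {16b} speaks of a run for every completed baseline, whereas {16c} has a person launch the script at intervals, so several people can be waiting, and under minimisation their order affects each one's chance of an offer.

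In an open trial, allocation concealment is the main protection against selection at entry. If work-ready people tended to enter when the intervention was favoured, the primary comparison would be biased, and adjustment for age, gender and pain duration would not remove it. The trial report would also carry a concealment claim stronger than the procedure supports.

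**Working it through.** The protocol gives no figure for predictability, so there is none to reproduce. The trial size used below does reproduce: (132 + 44 × 1.14) / 0.8 = 227.7, so 228 (Sample size {14}).

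**Step 1: can people be waiting together?** 228 entrants over one year with two launches a week is 228 / (52 × 2) = 2.2 per launch. Yes, if the script is launched only at the stated minimum.

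**Step 2: how predictable is the next assignment?** Inputs from the protocol are N = 228, two factors with three levels each, and a two-thirds coin. The gender and age mixes are assumptions; changing them barely moved the results. The guesser is assumed to know all earlier allocations and the next person's gender and age band. Let q be the probability of intervention and w(q) the share of assignments made at that q. Then

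accuracy = Σ w(q) × max(q, 1 − q).

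The protocol does not say how unequal allocation enters the algorithm, so four readings were simulated. The worked sums use an assumed gender mix of 30/69/1% and age mix of 15/45/40%.

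- **(a) Two equal groups**, the literal reading of {16a}. A group is favoured at 86.6% of assignments: 0.866 × 2/3 + 0.134 × 1/2 = 0.644, against 0.50 by chance. With another imbalance measure and mix, a group is favoured at 70.4%: 0.704 × 2/3 + 0.296 × 1/2 = 0.617.
- **(b) One in three, as three equal slots.** q takes the values 1/6, 1/3, 5/12 and 2/3: 0.555 × 0.833 + 0.046 × 0.667 + 0.164 × 0.583 + 0.235 × 0.667 = 0.746 (simulated 0.747), against 0.667 for always guessing control.
- **(c) 1:3, as four equal slots.** q runs from 1/9 to 2/3: 0.615 × 0.889 + 0.021 × 0.75 + 0.069 × 0.704 + 0.141 × 0.611 + 0.154 × 0.667 = 0.800 (simulated 0.802), against 0.75.
- **(d) Two groups, plain two-thirds coin, imbalance weighted to the target ratio** (run with other assumed mixes). Target 1/3: simulated 0.645 against 1 − 0.371 = 0.629. Target 1/4: 0.661 against 1 − 0.343 = 0.657.

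The gain is therefore about 12 to 14 points in (a), 8 in (b), 5 in (c) and 0 to 2 in (d).

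**Step 3: what could ordering do?** Assume a deliberate strategy. Three people are always waiting, and a favoured 20% are held back until the algorithm leans towards intervention. Let s_F and s_N be the shares of favoured and other people who receive an offer. With an assumed 20-point difference in return to work between favoured and other people,

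bias = 20 × [0.2 s_F / (0.2 s_F + 0.8 s_N) − 0.2(1 − s_F) / (0.2(1 − s_F) + 0.8(1 − s_N))].

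| Reading | s_F | s_N | Bias (points) |
|---|---|---|---|
| (a) | 0.564 | 0.484 | 20 × (0.226 − 0.174) = 1.0 |
| (b) | 0.416 | 0.313 | 20 × (0.249 − 0.175) = 1.5 |
| (c) | 0.335 | 0.230 | 20 × (0.267 − 0.178) = 1.8 |
| (d), target 1/3 | 0.385 | 0.368 | 20 × (0.207 − 0.196) = 0.2 |
| (d), target 1/4 | 0.348 | 0.342 | 20 × (0.203 − 0.199) = 0.1 |

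The range is roughly 0 to 2 points, against the 20-point difference the trial is sized to detect.

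**The case against.** The script chooses the arm and the trial manager only starts it. At least a third of the probability always lies away from the favoured group. The two sections can also be reconciled: {16b} may mean that completed baselines are processed one after another, and {16c} how often the job is started. If the script already takes people in completion order, launch timing alone changes nobody's allocation. Details of queue order and logs may stand in the full protocol or operating procedures. All of this stands, so the point rests on the positive claim in {16b} and not on missing operational detail.

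A reader might go further and infer several things that the documents do not support:

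- **That the trial manager controls when people reach randomisation by chasing baselines.** The sentence "The trial manager will be responsible for reminding participants of data collection appointments" sits in a paragraph on adherence and dropout and does not mention the baseline questionnaire that precedes allocation.
- **That there is a motive.** The worry about throughput in Sample size {14} concerns people declining the intervention, and the stated response is to change the ratio.
- **That the trial manager knows everyone's gender and age.** This is an inference from the working group's data access in {19} and the eligibility call in {26a}; it is not stated.
- **That bias could reach about 5 points.** That figure, 20 × (2 × 0.617 − 1) = 4.7, needs complete steering and the assumed 20-point gap. It also needs equal groups, which the protocol holds only as a fallback.

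**Conclusion.** The statement in {16b} is too strong for the procedure in {16a} and {16c}. The next assignment is partly predictable to someone who knows the earlier allocations and the next person's gender and age band, and the text does not exclude influence through the order in which waiting people are processed. How predictable depends on an unstated choice: the gain over the best uninformed guess runs from 14 points down to almost nothing.

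The likely damage is small. Cohort consent and baseline completion precede allocation, and the primary outcome comes mainly from a registry. Deliberate ordering gives about 0 to 2 points of bias under assumptions that do not come from the protocol: the waiting queue, the favoured 20% and the 20-point prognostic gap. The documents support neither a finding that allocation is known in advance nor one that the primary result is compromised. The claim should be corrected and the procedure tightened, because both are cheap.

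**What to change.** In Implementation {16c}, have the existing script in TSD start automatically on each baseline submission or on a fixed timer, process participants strictly in baseline time-stamp order, and write each result to a locked log. The trial manager's role then begins with the invitation.

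In {16b}, replace the absolute claim with wording such as: allocation includes a random component and cannot be known with certainty before it is made. One line in {16a} should say how the unequal ratio enters the minimisation, since predictability depends on it.

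The cost is minor scripting work and a few reworded sentences. If recruitment is already complete, correct the statement in the trial report, say who launched the script and how often, and check from the time stamps that processing followed the order of baseline completion.

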#### Implementation {16c}

The trial manager will run the script at least twice a week, and in cases where cohort participants are allocated to the intervention, the trial manager will retrieve contact information and give an invitation to participate in the intervention (see SPIRIT item 26a).

### Assignment of interventions: blinding

#### Who will be blinded {17a}

Participants receiving the intervention, study staff directly involved in the trial, and placement providers cannot be blinded due to the nature of the study. It will not be possible to blind the trial statistician to allocation status, due to the nature of sub-sampling 1:3 to be offered the intervention. In the case we switch to 1:2 randomisation, and groups are balanced, the statistician will be blinded.

#### Procedure for unblinding if needed {17b}

Not applicable as participants and study staff cannot be blinded.

### Data collection and management

#### Plans for assessment and collection of outcomes {18a}

The planned time points and methods for outcome data collection are summarised in Table 1, with detailed information regarding primary and secondary outcome measures provided in SPIRIT item 12. Participants will be offered to complete self-reported measures in English or Norwegian (based on the preferred language as stated when providing informed consent) and on paper (by postage) or in a digital format (by email) using Nettskjema. If the measures are completed using Nettskjema, we will receive complete data as questionnaire items are mandatory. Measures conducted on paper will be entered independently by two research team members. For our primary outcome of sustained return to work, we plan to use registry data from NAV, although we could use our own questionnaire data, in the case of missing registry data. For details of care received and services used, we will use registry data. The process evaluation will utilise a mix of data (see SPIRIT items 12 and 19) collected from the questionnaires, expression of interest forms (with consent), and registry data in addition to field notes, qualitative interviews with participants, case managers, placement managers, and diary records.

#### Plans to promote participant retention and complete follow-up {18b}

We have several strategies to promote participant retention, including strategies noted in SPIRIT item 11c. Case managers are important to promote retention as they will give support and aid participants in the intervention. We will give participants the option to receive their questionnaires either on paper or digitally. High street vouchers will be provided for all participants (both those in only the cohort and those offered the intervention), and travel expenses to work placements will be reimbursed for the intervention group [67]. Calls and reminder letters/emails will be used to encourage data return at all time points [68, 69].

### Data management {19}

The project will generate a mix of primary electronic and paper data, which will be retained for a minimum period of 10 years after study completion. Case report forms will be developed to collect all required study data. All electronic data will be collected using Nettskjema, which is a data collection system that ties to TSD (Service for Sensitive Data, UiO Oslo) using AES-256 encryption with public key technology, on which the Stata instance will run our script to manage and randomise. Paper-based forms, case report forms and the trial master file will be stored (deidentified) at Kristiania University College (KUC) in a locked filing cabinet and a restricted access room for a minimum period of 10 years. Questionnaires retrieved by post will manually be entered in a dummy Nettskjema form to ensure all data are gathered and securely stored in TSD. Our script merges each response from Nettskjema (expression of interest, consent, baseline, and follow-up) into a set of encrypted files containing contact information, consent responses and other directly identifiable data, and a pseudonymised data file merging baseline and follow-up responses, removing and transferring identifiable data before encrypting these as separate files. Data stored at TSD will be accessible by the trial working group and the trial statistician at Oslo Metropolitan University (OsloMet). The statistician at OsloMet will use the Stata software provided by TSD so that data never need to leave the TSD environment. Registry data will be retrieved as encrypted files directly into TSD from the given registry. Data collected by qualitative methods (focus group and individual interviews) will first be transcribed, then stored digitally (anonymised) in TSD for analysis using the NVIVO software (also via TSD infrastructure). We will explore using TSD’s dictaphone app (‘Nettskjema-diktafon’) which encrypts the file on the phone/tablet and sends the file to TSD for transcription and analysis. If the dictaphone app is sufficiently accurate, we will use this software; if not, we will use professional transcription services, anonymising transcripts. In this case, digital recordings of audio interviews will be securely erased immediately following approved transcription and electronic copies of transcripts will be stored in the TSD. Data Processing Agreements exist between KUC and OsloMet, and KUC and Manpower. Personally identifiable data will need to be shared between KUC and Manpower (e.g. to facilitate matching placements by providing details of the participants to be placed). Data shared between KUC and OsloMet will be pseudonymised. Sharing of data between KUC, Manpower, and case managers will be done using asymmetric encryption, where each team has a corresponding private decryption key. Data will be owned by KUC.

### Confidentiality {27}

We will take several steps to maintain confidentiality. All study staff and investigators will protect the rights of the trial’s participants to privacy and informed consent. All information collected will be handled strictly in accordance with the consent provided, always adhering to the GDPR and to Good Clinical Practice standards. The study has been approved by the Norwegian Regional Committee for Medical and Health Research Ethics (Reference no. 402918), and a Data Protection Impact Assessment has been conducted to safeguard privacy in collaboration with the Norwegian Centre for Research Data. The data management plan noted in SPIRIT item 19 will ensure confidentiality in the data collected.

### Plans for collection, laboratory evaluation, and storage of biological specimens for genetic or molecular analysis in this trial/future use {33}

This trial does not involve the collection, laboratory evaluation, and storage of biological specimens.

### Statistical methods

#### Statistical methods for primary and secondary outcomes {20a}

A detailed statistical analysis plan has been finalised and agreed prior to analysis by the research team. We will report all participant flow in line with the CONSORT guideline extension for reporting RCTs conducted using cohorts and routinely collected data showing withdrawal and loss to follow-up [15]. Analyses will be conducted within TSD using Stata v17 or above (Stata Corporation, College Station, TX). Participant characteristics and outcomes will be summarised as mean and standard deviation for normally distributed continuous data or with median and ranges for data with skewed distributions or counts and percentage for categorical data. The primary analysis approach will be ‘intention-to-treat’. To account for the trial design featuring clustering in the intervention arm, generalised linear (GLM) mixed effects models will be used to estimate the between-group differences for both primary and secondary continuous outcomes, adjusting for age, gender, and duration of pain, with a random intercept for case manager. For example, we will analyse the between-group differences in sustained return to work (a binary outcome) using a generalised mixed-effect model with logit link function, the above covariates, and fitting a random effect in case manager allocation.

Secondary outcomes will also be analysed using generalised mixed models, using link functions appropriate to the outcome (e.g. where outcomes are continuous, we will use a canonical link function). In all cases, we will adjust for the same covariates (i.e. age, gender, and duration of pain). The adjusted treatment effect estimates (mean difference) between the groups will be presented as point estimates within a 95% confidence interval. Our outcome measures are largely independent and no correction for multiple testing will be done. *P*-values < 0.05 will be considered statistically significant. All tests will be two-sided.

An economic evaluation will be conducted from the personal social services perspective [70]. At 3, 6, and 12 months post-randomisation, we will also use registry data to estimate hospital and community health and social care resource use. Current Norwegian unit costs will be applied to value total resource use in both groups. Responses to the EQ-5D-5L and SF-12 will be converted into multi-attribute Norwegian utility scores [71, 72]. Results will be presented using incremental cost-effectiveness ratios and cost-effectiveness acceptability curves. This accommodates sampling uncertainty and varying levels of willingness to pay for an additional quality-adjusted life year. We will consider a decision-analytical model to determine the expected costs and consequences of the intervention arm and care as the usual arm.

The process evaluation will use both quantitative and qualitative analysis. To investigate the mechanisms of sustained return to work, we will collect qualitative data from two to three focus groups with participants, individual interviews with case managers and placement managers, field notes, and observation techniques. The analysis of qualitative data will be thematic, and we will use the framework method in which data obtained during the intervention will be used to help build the thematic framework, using the software package NVivo (QSR International, Victoria) [73]. Quantitative data from the trial will be used to model predictors of joining the cohort and intervention, using anonymised NAV routine data (e.g. demographics, length of unemployment, and type of employment) and data from questionnaires (e.g. health-related quality of life and dimensions of work ability). Potential predictors will be selected through a trial managing group brainstorming session following a review of the available variables. Potential predictor variables will first be correlated in matrices and any highly colinear variables removed. We will then fit crude logit models, in which joining the intervention will be the outcome. Significant variables will subsequently be entered into adjusted logit models with a view to building a model with respect to both model parsimony and variance explanation.

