It is not clear how to best help unemployed people with persistent pain return to work (RTW). In Norway, usual care for people with persistent pain is interdisciplinary, featuring pain management services supported by physicians, psychologists, physiotherapists, and nurses [10]. Employment services in Norway take an individualised approach, often including assessments of work ability, training, and vocational rehabilitation programmes involving traineeships in sheltered businesses [11]. However, these services are not specifically tailored for people with pain. Effective vocational rehabilitation requires a combination of work-focused healthcare and supportive workplaces; unfortunately, the two are generally not coordinated [12]. Without intervention, return to work is unlikely after 2 years of unemployment [13]. Return to work rates for traditional vocational rehabilitation in the unemployed (rather than sick-listed) pain population are unclear. In 2020, we described the results of a feasibility study, done in the English Midlands, of an adapted supported work placement intervention, which featured work placement provision with case management support [13]. In this study, case managers were trained to act as a bridge between systems and institutions (e.g. between health care providers and the workplace), engage people about obstacles to work, and collaboratively agree on a return-to-work plan. We also provided supportive work placements. The developed intervention was acceptable and valued by the people involved, with around 20% of the sample obtaining paid employment within the short 6-month follow-up. The study suggested that self-perception of satisfactory functioning in role as well as management of identified obstacles may be key to increasing confidence for this group. As the study focused on feasibility, the effectiveness and cost-effectiveness of the intervention are still unknown.

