At baseline, we will collect demographic data and details of health care use in the past 3 months as well as health-related outcomes using the following validated questionnaires, which will be offered in Norwegian or English as preferred: health-related quality of life (EQ-5D-5L) [37, 38], the Warwick-Edinburgh Mental Well-being Scale [34, 39], PROMIS-29 [40, 41], and the Work Ability Score (as a single item taken from the Work Ability Index) [42, 43]. The EQ-5D-5L has been translated into Norwegian using the EuroQul Group translation methodology and Solberg et al. concluded that the instrument is reliable [44, 45]. Garratt et al. compared the EQ-5D-5L to the EQ-5D-3L, which has undergone limited evaluation in Norwegian patients with LBP, to examine floor and ceiling effects, response consistency, and concurrent validity, and found the 5L preferable to the 3L [46]. Garratt et al. have also reported Norwegian population norms for the instrument [47]. Work to determine a Norwegian value set is ongoing and anticipated to be available by the end of the trial [37]. Smith et al. did a confirmatory factor analysis and examined criterion validity and measurement invariance of their Norwegian version of the WEMWBS, reporting that it appears to measure mental well-being well and commending it for use [48]. Garratt et al. reported the Norwegian version of the PROMIS-29 to be a reliable and valid generic self-reported measure of health in the Norwegian general population, having done confirmatory factor analysis to assess structural validity and also examining concurrent validity [49]. The Work Ability Score item in Norwegian to our knowledge has not undergone any formal validation work, which we will acknowledge as a limitation. However, normative data from the Norwegian general population for the question is available for comparison [50].

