We will collect follow-up data at 3, 6, and 12 months from baseline measurement, where we additionally will ask about return to work, job offers, or usual care and services, and then, for those who have returned to work: satisfaction with work, the Work Role Functioning Questionnaire (WRFQ) [51, 52], and return to work self-efficacy [53–55] whether work makes the pain worse, healthcare and social care use, medication, and the amount of time they have been at work (Table 1). The WRQF has been cross-culturally adapted into Norwegian using guidelines proposed by Beaton et al. [56, 57]. Johansen et al. examined the internal consistency reporting Cronbach’s alpha coefficients for sub-scales were well-zoned, ranging between 0.80 and 0.90 [57]. The return-to-work self-efficacy scale has been translated into Norwegian and been assessed using principal components analysis, in addition to studies of internal consistency and concurrent validity. Cronbach’s alpha was high enough to indicate the potential for redundant items, although PCA outlined a three-factor structure matching the original instrument. The authors conclude that the instrument has satisfactory cross-cultural validity [55].

In general, there is an absence of work
examining reliability and responsiveness of these instruments, which we will
acknowledge as a limitation.

**Table 1 Tab1:** Outcome domains, measurement instruments, and measurement time points

Domain	Measurement instrument or key items within the questionnaire package	Abbreviation	T0	T1	T2	T3
Demographic	N/A		X			
Pain	Troublesome grid		X			
	Pain duration		X			
Work-related baseline	Educational level		X			
	Unemployed duration		X			
	Looking for work duration		X			
	Reasons for wanting to RTW		X			
Health-related quality of life	Health-related quality of life	EQ-5D-5L	X	X	X	X
	Warwick-Edinburgh Mental Well-being Scale	WEMWBS	X	X	X	X
	Patient Reported Outcome Measurement Information System 29	PROMIS 29	X	X	X	X
	Pain intensity		X	X	X	X
Details of care received and services used	Registry data: Norwegian patient register, Municipal patient and user register, and Control and payment of health reimbursements		X	X	X	X
	Received any care or help for pain last three months* or since the last questionnaire		X*	X	X	X
	List of used medications in last three months* or since the last questionnaire		X*	X	X	X
Work-related	Dimensions of Work Ability		X	X	X	X
	Confidence in RTW		X	X	X	X
	RTW self-evaluation		X	X	X	X
	Job offers			X	X	X

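### The fixed covariate list leaves each continuous secondary outcome unadjusted for its own baseline value, which costs precision but does not bias the comparison

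*Protocol article*

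**What the plan says.** The statistical methods section {20a} describes mixed models for the primary and the continuous secondary outcomes, "adjusting for age, gender, and duration of pain, with a random intercept for case manager". For secondary outcomes it then repeats the list as a rule: "In all cases, we will adjust for the same covariates (i.e. age, gender, and duration of pain"). Results are to be reported as follows: "The adjusted treatment effect estimates (mean difference) between the groups will be presented as point estimates within a 95% confidence interval". The section mentions no change score, no model with baseline as a response, and no other use of T0 values.

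The baseline values will exist. The text before Table 1 says: "At baseline, we will collect demographic data and details of health care use in the past 3 months as well as health-related outcomes". Table 1 ("Outcome domains, measurement instruments, and measurement time points") marks EQ-5D-5L, WEMWBS, PROMIS-29, pain intensity, work ability and confidence in return to work at T0 and at all three follow-ups. By contrast, the Work Role Functioning Questionnaire (WRFQ), satisfaction with work, pain interference with work and work pattern are marked only at T1 to T3, for those who return to work.

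Minimisation, under Sequence generation {16a}, uses gender and age only.

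**The concern.** A participant's own baseline score usually carries information about the follow-up score that age, gender and pain duration do not. If it is left out, that explainable variation stays in the residual. Confidence intervals are then wider than they need be, and any chance difference between arms at baseline passes in part into the estimated effect. Minimisation does not balance these scores, and the intervention arm is small, so such differences will not be rare.

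The secondary outcomes are at stake. Each is compared at 3, 6 and 12 months, with p below 0.05 called significant and no multiplicity correction. The data needed for the better analysis are already being collected.

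This is a stated choice and not a detail left to the SAP, because the protocol gives a closed list and applies it to every case. An SAP that adds baseline values would contradict the protocol sentence.

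**Working it through.** **Inputs.** From Sample size {14}: 132 control and 44 intervention participants with data, 10% versus 30% sustained return to work, 80% power, 5% significance, 20% loss and a design effect of 1.14 in the intervention arm. From {20a}: two-sided tests. Assumed, because the protocol gives no value: baseline to follow-up correlation r of 0.3, 0.5 or 0.7. Strictly, r is the partial correlation given age, gender and pain duration.

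**The plan's own figure.** The two-proportion formula with continuity correction at 1:3 gives 44 + 132 = 176, as stated. Inflation gives (132 + 44 × 1.14) / 0.80 = 182.16 / 0.80 = 227.7, so 228, as stated. The point below does not affect this calculation.

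**Precision without the baseline value.** In SD units, the standard error of a difference in means is √(1/132 + 1/44) = 0.174. The detectable difference is (1.960 + 0.842) × 0.174 = 0.488 SD.

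**Precision with the baseline value.** Residual variance is multiplied by 1 − r², so the detectable difference and the confidence interval width are multiplied by √(1 − r²).

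| Assumed r | 1 − r² | Variance ratio 1/(1 − r²) | Detectable difference | Power for 0.488 SD | 176 adjusted participants are worth |
|---|---|---|---|---|---|
| none | 1 | 1 | 0.488 SD | 80% | 176 |
| 0.3 | 0.91 | 1.10 | 0.465 SD | 84% | 193 |
| 0.5 | 0.75 | 1.33 | 0.422 SD | 90% | 235 |
| 0.7 | 0.51 | 1.96 | 0.348 SD | 98% | 345 |

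The ratios do not depend on 132 and 44; the detectable differences do.

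**Chance imbalance.** A baseline score has the same standard error for its between-arm difference, 0.174 SD. An imbalance of 0.2 SD or more has |Z| above 0.2 / 0.174 = 1.15, a probability of about 25% per outcome. Without adjustment, a 0.2 SD imbalance moves the estimate by r × 0.2, which is 0.06, 0.10 or 0.14 SD. This is the same variance as in the table seen from another side (r² × 0.174² is what adjustment removes), so it is not an additional loss.

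**Unemployment duration in the primary model.** Table 1 records "Unemployed duration" at T0, but it is not a covariate. Expected events are 0.10 × 132 + 0.30 × 44 = 26.4. Ordinary logistic regression without a random effect was simulated at n = 176, with 2,000 runs per setting. Adding a covariate with an assumed log odds ratio of 0.5, 0.75 or 1.0 per SD moved power from 86.7% to 87.9%, from 85.6% to 87.2%, and from 86.5% to 89.1%. The gain is about 1 to 3 points.

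**The case against.** The article condenses a fuller plan. It says a detailed SAP has been finalised, and that document is not shown. One could read the shared covariates as the set common to all outcomes, with each outcome's own baseline added separately, or suppose that changes from baseline are analysed, since the outcomes section speaks of changes in quality of life. Neither is the natural reading of a list that is spelled out and applied to all cases, and {20a} mentions neither. A change score would not close the gap either. With equal SDs at both times its variance factor is 2(1 − r), which is 1.40, 1.00 or 0.60 at r = 0.3, 0.5 or 0.7, against 0.91, 0.75 or 0.51 with baseline adjustment.

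The size of the gain rests on an assumed correlation, and at 0.3 it is modest. That stands, and is why a range is shown.

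A reader might go further and infer that leaving out unemployment duration biases the primary estimate, because the background says: "Without intervention, return to work is unlikely after 2 years of unemployment". The protocol does not support this. Allocation is randomised, so omitting a prognostic factor does not bias the comparison on average, and the confidence interval already allows for chance imbalance. The background sentence suggests prognostic value but makes no commitment to adjust. The primary model ("using a generalised mixed-effect model with logit link function, the above covariates, and fitting a random effect in case manager allocation") already has about five fixed parameters: treatment, age, two for gender on three levels, and pain duration. With about 26 events that is 26/5 = 5.2 events per parameter, and a sixth makes it 26/6 = 4.3. There is also a random effect for only two to four case managers. In a logistic model an added prognostic covariate also changes the conditional odds ratio being estimated. A short list is defensible there.

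Nor does the point extend to every analysis. The measures confined to those who return to work have no T0 value, and the Harms section deliberately leaves harms unadjusted.

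**Conclusion.** The point holds for continuous secondary outcomes with a T0 value: EQ-5D-5L, WEMWBS, PROMIS-29, pain intensity, work ability and confidence in return to work. The stated rule discards baseline information that is already collected. At 132 versus 44, and for an assumed correlation of 0.3 to 0.7, the unadjusted analysis has 1.10 to 1.96 times the residual variance. It can detect 0.488 SD where 0.465 to 0.348 SD would be within reach. Chance baseline imbalance is left uncorrected.

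The loss is one of efficiency. The randomised comparison stays valid and unbiased on average, and neither the sample size nor the primary result is touched. It is worth correcting, but it does not threaten the trial.

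**What to change.** Replace the covariate sentence in {20a} with wording to this effect: *each continuous secondary outcome is adjusted for its own baseline (T0) value, where one is collected, plus age, gender and duration of pain.* For PROMIS-29 this means the baseline score of the same domain. State that WRFQ, satisfaction with work, pain interference with work and work pattern keep the present covariates, because they have no baseline.

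Make the change in the protocol, and in the SAP if it repeats the closed list, before outcome data are seen; a later choice would look post hoc. No new data are needed, and each affected model gains one parameter. Randomisation follows completion of the baseline questionnaire, so few baseline values should be missing.

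Adding unemployment duration to the primary model is optional. If it is wanted, pre-specify it as a single continuous term and weigh the small gain against the roughly 26 expected events.
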